#### Sample size justification

There is no definitive guidance relating to sample sizes in pilot and feasibility studies with a heuristic of 30 (range=10–40) patients generally applied. Therefore, no formal sample size calculation has been performed for the feasibility study. To allow for a 15% attrition rate, a minimum sample of 35 patients will be recruited, allowing recruitment and retention rates to be estimated with 95% CI maximum widths of 2% and 28%.^30^

#### Data analysis

Simple descriptive statistics will be reported for each feasibility outcome measure (eg, number and proportion of eligible participants enrolled). All quantitative analyses will be conducted in SPSS or STATA. Interim analyses will be conducted 6 months after opening the study to recruitment.

Data will be collected from Atom5™ to assess the feasibility and acceptability of the PRO-CAR-T digital platform and *a priori* benchmarks applied:

Retention: Number and proportion of patients who complete the 12-month PRO assessment. The study will be considered feasible if 
≥
70% of patients complete the final assessment at month 12.Adherence: Number and proportion of patients completing the PRO assessments. The study will be considered feasible if 
≥
70% of expected PRO assessments are completed at each time point, taking into consideration attrition arising from disease progression, severe toxicity resulting in loss of capacity or death. We will document reasons for non-completion (eg, hospital admission). Missed completions will be checked against the patient’s medical notes by a member of the clinical team (ie, research nurse) to identify possible reasons for non-completion (ie, a record of ICANS or other severe adverse treatment-related events, hospital admission or death). To be considered adherent, patients will need to have submitted their report via the PRO-CAR-T system within 72 hours of the scheduled time point. *Ad hoc* reports will not contribute to the assessment of adherence. Incomplete submissions will be accepted, although missing data are expected to be minimal with the required fields functionality in Atom5.Recruitment: Number and proportion (%) of eligible patients who consent to take part. The study will be considered feasible if 
≥
50% of eligible patients consent.

Number of clinical alerts and number and proportion of patients reporting clinical alerts.Number and proportion of patients who withdraw formally from the study and their reasons for withdrawal.Actions arising from alerts including number and proportion of patients attending clinic, hospitalisation following clinical alert reporting, estimated time between alert and response by clinical team.Number of *ad hoc* PRO assessments completed and the number and proportion of patients submitting ad hoc PRO assessments.

At 3, 6 and 12 months postinfusion, acceptability will be assessed using implementation outcome measures: Acceptability of Intervention Measure (AIM), Intervention Appropriateness Measure (IAM) and Feasibility of Intervention Measure (FIM) scales. Psychometric evaluation showed acceptable internal consistency reliability (Cronbach’s alpha values ranging from 0.85 to 0.91) and test–retest reliability (Pearson correlation values ranging from 0.73 to 0.88), and a Flesch 5th reading grade level score. Each scale has four items and completion time for all three scales is less than 5 min. Participants will rate their agreement on a Likert scale in response to statements about using the PRO-CAR-T digital system (eg, ‘The PRO-CAR-T system is appealing to me.’).^31^

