### WP 3: feasibility study

The PRO-CAR-T feasibility study is a single-centre study of the feasibility and acceptability of the new ePRO system when deployed in the UK’s NHS. 30 CAR-T patients will be recruited consecutively to use the PRO-CAR-T system (ie, in addition to usual care). Patients who consent to participate will be onboarded to the system prior to infusion. During the baseline visit, participants will download the Atom5 app to their mobile device, give their demographic details including age, sex at birth, ethnicity, cancer diagnosis, CAR T-cell therapy, and self-reported experience with technology and complete the PRO measures for the first time. PRO measures will be completed subsequently via the PRO-CAR-T system at prespecified intervals (measures and frequency of assessments will be established in WP 1). We will follow participants for 12 months from date of infusion (day 0) to understand the feasibility and acceptability of longitudinal collection of PROs for CAR-T patients, their families and HCPs. The findings will be used to inform a future, definitive RCT to assess the effectiveness of remote symptom monitoring using the digital system alongside usual care compared with usual care alone.

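### The 70% retention benchmark states no allowance for death, progression or loss of capacity, while the 70% adherence benchmark covering the same month-12 assessment does, so retention could be missed for reasons unrelated to the ePRO system

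*Protocol article*

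**What the plan says.** The Data analysis section of WP 3 in the Protocol article sets benchmarks in advance for retention, adherence and recruitment, each with its own statement of when the study counts as feasible.

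- Retention is given as "Retention: Number and proportion of patients who complete the 12-month PRO assessment". The pass mark is that at least "70% of patients complete the final assessment at month 12". No group of patients is removed from the denominator.
- Adherence also has a 70% pass mark. It applies to expected assessments at each time point, "taking into consideration attrition arising from disease progression, severe toxicity resulting in loss of capacity or death". A 72-hour submission window is stated for adherence only.

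Two other sections bear on the denominator. The Sample size justification says "To allow for a 15% attrition rate, a minimum sample of 35 patients will be recruited"; it does not say what the 15% consists of. The WP 3 feasibility study section says "Patients who consent to participate will be onboarded to the system prior to infusion", while follow-up is counted from the day of infusion. That section also says "30 CAR-T patients will be recruited consecutively to use the PRO-CAR-T system", so the check below uses 35 and repeats the key figures for 30.

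**The concern.** Month 12 is one of the time points at which adherence is judged. One assessment is therefore judged twice at the same 70% threshold. Losses to death, progression and incapacity are taken into account once and, on the plain wording, not taken into account the other time. The plan does not say which result governs if they disagree.

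The adherence wording shows that the authors regard these losses as no reflection on the system. Retention, as worded, mixes them with the losses that do reflect on it, such as disengagement and withdrawal. The introduction describes toxicities that can threaten life, so some disease-related loss over 12 months is foreseeable. A retention result below 70% could then be read as patients giving up on the system when they had died or become unable to report. That reading would carry into the design of the definitive RCT, which this study is meant to inform.

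There is also a smaller gap at the start of follow-up. A patient who consents and is onboarded but never infused has no month-12 time point, and the wording does not say whether that patient counts.

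**Working it through.** **Inputs.** Sample size 35, 15% attrition (Sample size justification); 30 patients (WP 3: feasibility study); 70% pass mark for both benchmarks (Data analysis). The document gives no 12-month rate of death, progression or incapacity.

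**Step 1: the plan's own figure.** 30 × 1.15 = 34.5, which rounds up to the stated 35. Dividing instead, 30 / 0.85 = 35.3, gives 36. Either way the stated number is essentially reproduced, and 35 × 0.85 = 29.75, so about 30 patients would remain.

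**Step 2: what the retention rule requires.** 0.70 × 35 = 24.5, so 25 completers are needed and at most 10 losses of any cause are tolerated. For 30 patients, 21 are needed and 9 losses are tolerated.

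**Step 3: link between the two benchmarks.** Let *a* be the proportion lost for reasons that adherence excuses, and *c* the proportion of the remaining patients who complete month 12. Then

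expected retention = (1 − *a*) × *c*, and the *c* needed for 70% retention = 0.70 / (1 − *a*).

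Assume that the whole 15% is excused loss. Then *c* must be 0.70 / 0.85 = 82.4%. To reach 25 of 35 it must be 25 / 29.75 = 84.0%. On the adherence denominator the same patients need only 70%.

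**Step 4: chance of passing.** This is the binomial probability of at least 25 successes in 35 with success probability (1 − *a*) × *c*. Each cell shows expected retention and, in brackets, that chance. The 15% row uses the plan's figure under the assumption above; the other loss rates are assumptions chosen to show the range.

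| Excused loss *a* | *c* needed | *c* = 80% | *c* = 90% | *c* = 100% |
|---|---|---|---|---|
| 10% | 77.8% | 72.0% (0.614) | 81.0% (0.945) | 90.0% (1.000) |
| 15% | 82.4% | 68.0% (0.408) | 76.5% (0.820) | 85.0% (0.989) |
| 20% | 87.5% | 64.0% (0.232) | 72.0% (0.614) | 80.0% (0.925) |
| 25% | 93.3% | 60.0% (0.112) | 67.5% (0.384) | 75.0% (0.758) |
| 30% | 100% | 56.0% (0.046) | 63.0% (0.197) | 70.0% (0.510) |

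With 30 patients and 21 needed, the 15% row gives 0.494, 0.854 and 0.990, so the choice between 30 and 35 does not change the picture.

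**Step 5: the disagreement.** At 15% excused loss and 80% completion of the remainder, month-12 adherence is 80%, which clears its benchmark (taking all reports as within 72 hours). Expected retention is 68%, which misses. The completion that retention demands rises with the rate of disease-related loss; the adherence requirement stays at 70%.

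**The case against.** Retention and adherence are different outcomes. Retention in everyone enrolled is useful for planning an RCT, and passing one benchmark while missing the other can be informative. The plan already records reasons for non-completion, checks missed reports against the notes and reports withdrawals with reasons, so a careful reader could separate deaths from disengagement. The text does not say outright that deaths count as retention failures; that follows from an unqualified denominator. A patient whose disease progresses but who completes month 12 is retained. All of this stands. It supports keeping the all-enrolled figure, but not using it unqualified as a feasibility verdict.

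Several stronger readings are tempting, and the document does not support them.

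- *A system that meets the plan's own assumptions would fail.* The only numerical assumption is 15% attrition. If that is total loss, retention is 85% and the chance of passing at n=35 is 0.99.
- *The plan implies 0.85 × 0.70 = 59.5% retention, with a 0.10 chance of passing.* This treats the 70% pass mark as an expected completion rate and takes all 15% as excused loss. If the 15% is already total loss to month 12, it counts loss twice. It also ignores that a late month-12 report fails the 72-hour window but can still count for retention.
- *Retention would largely measure survival.* The 54.4% in the Introduction is a complete-response rate, not a 12-month survival figure.
- *The benchmark is out of reach at 30% loss.* At that assumed rate the chance of passing is 0.20 with 90% completion and 0.51 with full completion.
- *Missing one benchmark makes the whole study infeasible.* No such rule is stated.

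**Conclusion.** The point holds in a limited form. Two adjacent benchmarks judge the month-12 assessment at 70%. Only one states an allowance for death, progression and loss of capacity, so a pre-stated retention verdict would partly reflect disease-related loss rather than use of the system.

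Under the assumption that the 15% attrition is all excused loss, retention needs about 82% completion among the remaining patients (84% for 25 of 35), against 70% for adherence. At 80% completion the chance of passing is 0.41; at full completion it is 0.99. The system could miss the benchmark; nothing in the document shows that it would. How large the effect will be cannot be settled from the document, because it gives neither the causes of the 15% nor a 12-month loss rate.

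This is a moderate point about how a decision rule is defined. It should be settled before results are seen, but it does not undermine the study.

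**What to change.** Apply the 70% retention benchmark to infused participants still expected to report at month 12. Use one definition of the allowance for retention and adherence: death, and progression or documented loss of capacity that prevents reporting. Patients who withdraw formally or simply stop reporting stay in the denominator as not retained. Progressed patients who do report count as retained.

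Beside it, report the proportion of all enrolled patients who complete month 12, as a descriptive figure for planning the RCT. Split the losses by cause: death, progression, loss of capacity, non-infusion, withdrawal and other non-completion.

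A denominator limited only to infused patients alive at month 12 would not be enough, because it would still count as failures the progression and incapacity that adherence takes into account.

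The cost is revised outcome wording and a small table. Much of the information is already to be collected, since missed reports are checked against the notes and withdrawals are recorded with reasons. The denominator shrinks somewhat. At 15% excused loss it falls from 35 to about 30, and the 95% CI width at 70% retention, 2 × 1.96 × √(0.7 × 0.3 / n), rises from 30% to 33%. Retention and month-12 adherence would also become close to the same measure, differing mainly in the 72-hour window, and the plan should say so.

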#### Qualitative substudy

We will conduct a qualitative evaluation of the PRO-CAR-T system with clinicians and a subsample of feasibility study participants at approximately 3 months postinfusion. This time interval was selected to ensure patients have sufficient opportunity to use the PRO-CAR-T system. Patients and HCPs who give their consent to participate will take part in an interview lasting up to 1 hour, with breaks as required. Semistructured topic guides (tailored to the different participant groups) will be used to ensure key topics are consistently covered. The topic guides will remain flexible and evolve based on findings. We will use reflexive thematic analysis for data analysis in NVivo with two researchers coding a subset of the transcripts to cross check the coding strategy and data interpretation.

## Patient and public involvement

The patient and public involvement and engagement (PPIE) plan for the PRO-CAR-T study sits within the overall Blood and Transplant Research Unit (BTRU) PPIE strategy.^32^ The strategy has been developed by patients, carers, members of the public and researchers who have worked together to agree a PPIE action plan informed by the UK Standards of Public Involvement in Research.^33^ In accordance with principles of coproduction and the BTRU PPIE Strategy, researchers will work in partnership with patient and public contributors through a mix of consultation, collaboration and user-led activities.^32^ Patient authors have been involved in the codesign of the research protocol, patient and public-facing materials such as lay summaries and patient information leaflets. Future activities will include supporting the interpretation of findings, codesigning engagement strategies and materials to share findings with the public (eg, lay summaries, press releases, creative and social media communications), coauthoring academic/clinical outputs and supporting research governance activities (eg, patients and public contributors are included in the BTRU Project Management Group).

## Ethics and dissemination

Ethical approval for the study was provided by the UK’s Health Research Authority Social Care Research Ethics Committee B Proportionate Review Subcommittee (HSC REC B) (ref: 23/NI/0104). The results of the study will be published in a peer-reviewed journal, presented at conferences and symposia and shared with patients and members of the public through lay summaries via multiple media.
